### 4.8 Additional analyses

Subgroup analyses may be undertaken to explore potential differential impacts of therapies based on baseline characteristics such as age, severity of PMS symptoms, menstrual cycle regularity, or baseline psychological distress. Adjusted analyses using multivariate models may also be conducted to account for potential confounders (e.g., BMI, diet, baseline stress levels, or prior PMS-related therapies). These will be explicitly categorized as exploratory and interpreted cautiously. Interaction effects between CBT and *Brahmi* will also be examined if the sample size permits. Exploratory analyses may include treatment adherence, participant satisfaction, and patterns in biopsychosocial variables.

### 4.9 Analysis population and missing data

Both intention-to-treat (ITT) and per-protocol analyses will be presented. The ITT analysis will preserve the benefits of randomization and provide insights into real-world effectiveness, while per-protocol analysis will evaluate outcomes in participants with good adherence (≥ 80% intervention completion and no major protocol violations). Missing data will be managed using complete-case analysis as the primary approach. Sensitivity analyses, including last-observation-carried-forward (LOCF), will be performed to assess robustness. Multiple imputation will not be applied, consistent with recommendations for exploratory trials. Mixed-effects models with maximum likelihood estimation may be used for repeated assessments to account for missingness without formal imputation when appropriate. All statistical analyses will be performed using the latest versions of SPSS or R by an independent biostatistician, ensuring objectivity and scientific rigor.

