#### 4.2.2 Sample size

The proposed study is a randomized controlled exploratory trial aimed at providing preliminary insights into the comparative outcomes of two independent groups. As formal power calculations are not mandatory for exploratory studies, a two-sample t-test formula for comparing means was applied primarily to provide a rational basis for determining a feasible sample size:

$$n=\frac{2\,s_{p}^{2}\,{\left[Z_{1-\alpha /2}+Z_{1-\beta }\right]}^{2}}{\mu_{d}^{2}}$$

This formula incorporates the pooled variance, the anticipated mean difference between groups, the significance level (α), and statistical power (1−β). Using estimates from published data, the pooled variance (sp^2^) was taken as 2.85, and the expected mean difference (μd) between groups as 1.83. For reference, a two-sided test with a significance level of 0.05 (Z = 1.96) and a nominal power of 90% (Z = 1.28) was considered. Substituting these values yielded a preliminary estimate of approximately 18 participants per group. Allowing for an anticipated dropout rate of 20%, the adjusted number was approximately 23 participants per group, resulting in a total sample size of 46.

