#### 4.6.6 Retention

This study informs participants that their involvement is completely voluntary, and they may quit at any time without repercussions. If a participant opts to withdraw for any reason, their decision will be acknowledged. Efforts shall be undertaken to prevent unnecessary dropouts, where feasible. Participants who choose to withdraw will not be subject to any additional data collection or follow-up. This methodology guarantees compliance with ethical norms, honoring participants’ autonomy and rights during the research process.

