### 4.10 Safety

All adverse events (AEs) and serious adverse events (SAEs) will be systematically documented in the Case Report Form (CRF) using a predefined Adverse Drug Reaction (ADR) page. Each entry will capture the event description, diagnosis (if available), onset and resolution dates, severity (mild, moderate, or severe), action taken with the study drug (none, temporarily interrupted, or permanently withdrawn), outcome (resolved, resolved with sequelae, or not resolved), and the assessed relationship to the study drug (definite, probable, possible, unlikely, not related, or not assessable). The Principal Investigator and Co-Investigator will independently evaluate causality, taking into account the temporal relationship with the study drug, the participant’s clinical course, medical history, and concomitant medications. All adverse events will be followed until resolution or stabilization. Events occurring after a participant exits the study will not be routinely reported unless the investigators consider a reasonable likelihood of relation to the study drug, psychotherapy, or study procedures. This systematic documentation ensures continuous monitoring and prioritization of participant safety throughout the trial

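### Section 4.9 claims the benefits of ITT but makes complete-case analysis primary and leaves the mixed model it names optional; the arm comparison can be biased if dropout differs between arms

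*Protocol article*

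**What the plan says.** Section 4.9 sets the analysis populations: "Both intention-to-treat (ITT) and per-protocol analyses will be presented". It gives the purpose of the first: "The ITT analysis will preserve the benefits of randomization and provide insights into real-world effectiveness". On missing outcomes it then fixes the method: "Missing data will be managed using complete-case analysis as the primary approach". The check on that method is "Sensitivity analyses, including last-observation-carried-forward (LOCF), will be performed to assess robustness". Multiple imputation is ruled out. A mixed-effects model fitted by maximum likelihood is mentioned for the repeated assessments, but only as something that may be used where appropriate. Section 4.7 is equally open between ANOVA and mixed-effects models, and the abstract names repeated measures ANOVA.

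On the amount of missing data, section 4.2.2 says "Allowing for an anticipated dropout rate of 20" per cent, and raises 18 per group to 23. On women who leave, section 4.6.6 says "Participants who choose to withdraw will not be subject to any additional data collection or follow-up".

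**The concern.** Intention-to-treat keeps the comparison between the groups as randomised. A complete-case analysis compares the women who happened to finish. Where finishing is related to how a woman fared on her allocated treatment, and related differently in the two arms, the completers are no longer comparable groups. The claim about randomisation then fails for the analysis that is called primary.

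The plan itself expects a fifth of the women to leave. Adding participants for dropout restores precision but does nothing about bias. Section 4.7 makes effect sizes and 95% confidence intervals the main output, as signals for later confirmatory work, and these are the quantities that selective dropout distorts.

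The plan also collects data that would help. Sections 4.6.3 and 4.6.4 have the DRSP kept daily in screening cycles 1 and 2 and in treated cycles 3 and 4. A woman who leaves in cycle 4 has up to two untreated cycles and one treated cycle on record. Complete-case analysis discards them; a likelihood model uses them.

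**Working it through.** **1. The plan's own sample size.** Inputs from section 4.2.2: variance 2.85, difference 1.83, Z values 1.96 and 1.28, dropout 20%.
- n = 2 × 2.85 × (1.96 + 1.28)² / 1.83² = 17.87, so 18 per group.
- 18 / 0.80 = 22.5, so 23 per group and 46 in total. The stated figure reproduces.
- Expected leavers: 46 × 0.20 = 9.2. Expected completers: 46 × 0.80 = 36.8. So about 9 of 46 drop out of the primary analysis.

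**2. General form of the bias.** If a proportion p of an arm leaves, and leavers differ from completers by a gap g, then completer mean − full-arm mean = −p × g. The bias in the comparison is the difference of this term between arms.
- Same p and same g in both arms: zero.
- 25% against 15%, g = 0.5 SD in both: (0.25 − 0.15) × 0.5 = 0.05 SD.
- 30% against 10%, g = 1 SD in both: (0.30 − 0.10) × 1 = 0.20 SD.

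The protocol gives no dropout by arm or by reason, so these patterns are assumptions.

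**3. A strong one-arm scenario (assumed).** No true effect; 20% leave each arm; on Brahmi the leavers are the women worst in the first treated cycle, on placebo they are a random 20%. The correlation r between any two cycles is equal and is taken as 0.5 to 0.7.

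Removing the worst 20% shifts the mean of that cycle by φ(z)/0.8 = 0.35 SD. Then:
- unadjusted final score: 0.35 × r = 0.18, 0.21 and 0.25 SD (r = 0.5, 0.6, 0.7);
- adjusted for baseline, approximately: 0.35 × r × (1 − r) = 0.09, 0.08 and 0.07 SD;
- change from baseline: 0.35 × (r − r) = 0, because the selection shifts baseline and final means equally;
- LOCF: the leavers average 0.35 × 0.8 / 0.2 = 1.4 SD in the first treated cycle, and this is carried forward when r × 1.4 would be expected. The error is 0.2 × 1.4 × (1 − r) = 0.14, 0.11 and 0.08 SD, with the opposite sign.

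**4. Simulation of step 3.** 23 per arm, 5 leavers per arm, 4,000 trials per correlation. Negative values favour Brahmi.

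| Estimate | r = 0.5 | r = 0.6 | r = 0.7 |
|---|---|---|---|
| Complete-case, unadjusted | −0.18 | −0.22 | −0.25 |
| Complete-case, baseline-adjusted | −0.10 | −0.09 | −0.09 |
| LOCF | +0.14 | +0.11 | +0.08 |
| Maximum likelihood, using the first treated cycle | within 0.01 of 0 | within 0.01 of 0 | within 0.01 of 0 |

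The standard error of the likelihood estimate equals that of the baseline-adjusted complete-case estimate (0.24 to 0.30 SD for both), so the mixed model costs no precision.

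**5. Milder selection.** When leaving on Brahmi depends on symptoms only by probability, the baseline-adjusted complete-case bias is 0.05 to 0.07 SD. A separate run on the planning variance gave −0.10 units; with an SD of √2.85 = 1.69 that is 0.06 SD. When leaving depends on symptoms in the same way in both arms, the bias is about zero.

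**The case against.** **Size.** A reader might take 0.2 SD or more as the bias to expect. The documents do not support that. Section 4.1 defines the outcomes as changes, and section 4.7 includes baseline among the time points, so an unadjusted comparison of final scores is the least likely form of the analysis. With baseline used, the figure is about 0.1 SD or less, against a standard error of 0.24 to 0.30 SD. Nor does anything in the protocol suggest that Brahmi in particular would be favoured. This objection stands, and the size is stated accordingly.

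**Withdrawal.** A reader might infer that section 4.6.6 ends data collection once a woman stops tablets or CBT. It speaks of women who quit the study. Section 3.8.3 keeps partial adherents for sensitivity analysis, and section 4.10 records permanent withdrawal of the study drug as an action separate from leaving the study. What remains is a useful clarification.

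**Safety follow-up.** A reader might also see a contradiction between section 4.6.6 and the statement in section 4.10 that "All adverse events will be followed until resolution or stabilization". Section 4.10 goes on to limit the reporting of events after a participant exits to those with a reasonable likelihood of relation to the trial. At most there is a narrow ambiguity about an event still open when a woman withdraws, and it has no bearing on the efficacy analysis.

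**Preference and status.** The plan already names the mixed model, its list of sensitivity analyses is open-ended, model detail may sit in an analysis plan that is not shown, and the trial makes no inferential claims. The exploratory status does limit the consequence. The rest does not answer the point, because the protocol is not silent: it fixes the weaker method as primary and leaves the better one to later discretion.

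**Conclusion.** The point holds as an inconsistency within section 4.9 and a poor choice of primary method. About 9 of 46 randomised women would be expected to fall out of an analysis said to keep the benefits of randomisation.

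Bias arises only if dropout is related to outcome differently in the two arms. In that case it is about 0.1 SD with baseline adjustment and up to about 0.25 SD without, under an assumed strong one-arm selection and correlations of 0.5 to 0.7. It can go either way. In the same scenario LOCF is off by 0.08 to 0.14 SD in the other direction, so agreement or disagreement between the two would tell the reader little.

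The near-zero bias of the likelihood estimate rests on dropout depending on scores that were observed. Where it depends on unseen scores, some bias would remain under any of these methods. The consequence is for the effect sizes and intervals that the trial reports.

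**What to change.** **Section 4.9.** Make the maximum-likelihood mixed model named there the primary analysis. Include all randomised participants with any observed post-baseline outcome, analysed in the allocated arm, with terms for arm, cycle, arm-by-cycle and baseline score. For the DRSP, use the cycle scores from the daily diaries in cycles 3 and 4, so that the first treated cycle informs the estimate for women who leave later. Move complete-case analysis to a sensitivity analysis, and do not rely on LOCF as the robustness check. Describe the analysis set as it is: a woman with no post-baseline value still contributes nothing to the comparison.

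**Section 4.7 and the abstract.** Bring the wording on ANOVA into line.

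**Section 4.6.6 (minor clarification).** State that women who stop tablets or CBT without withdrawing consent are invited to continue the outcome assessments.

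**Cost.** Wording changes and slightly more modelling work. The sample size is unchanged, and the simulation shows no loss of precision.

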### 4.7 Exploratory statistical analysis

Exploratory statistical analysis will primarily explore the potential impact of Cognitive Behavioral Therapy (CBT) combined with either *Brahmi* (Bacopa monnieri) tablets or placebo in participants with moderate to severe Premenstrual Syndrome (PMS). Outcome measures include the Daily Record of Severity of Problems (DRSP), Quality of Life Enjoyment and Satisfaction Questionnaire (Q-LES-Q), and Sheehan Disability Scale (SDS), assessed at three time points: baseline (third visit), during treatment (fourth visit), and post-treatment (fifth cycle follow-up). Analyses will be descriptive, focusing on effect size estimates and 95% confidence intervals to provide insights into the direction and magnitude of observed effects. P values will be presented descriptively without inferential claims, in line with the exploratory nature of the study. Where appropriate, repeated measures approaches such as ANOVA or mixed-effects models may be applied to summarize changes over time and between groups, with emphasis placed on effect size interpretation to generate preliminary signals for future confirmatory research.

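### Section 4.9 names maximum likelihood for the optional mixed model; with 18 to 23 women per arm, 95% intervals from that model would be about 2–3% too narrow

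*Protocol article*

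**What the plan says.** Section 4.9 fixes the main handling of missing data: "Missing data will be managed using complete-case analysis as the primary approach". Last observation carried forward is a sensitivity analysis, and multiple imputation is ruled out. It then adds: "Mixed-effects models with maximum likelihood estimation may be used for repeated assessments to account for missingness without formal imputation when appropriate". This is the only place where the article names an estimator for a mixed model. The same section names SPSS or R as software.

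Section 4.7 describes the outcomes as "assessed at three time points: baseline (third visit), during treatment (fourth visit), and post-treatment (fifth cycle follow-up"). On modelling it says: "Where appropriate, repeated measures approaches such as ANOVA or mixed-effects models may be applied to summarize changes over time and between groups". On output it says: "Analyses will be descriptive, focusing on effect size estimates and 95% confidence intervals", and adds: "P values will be presented descriptively without inferential claims". The abstract names repeated measures ANOVA and sets a 0.05 significance level.

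Section 4.2.2 derives about 18 women per group before dropout and 23 after allowing for 20% dropout, "resulting in a total sample size of 46".

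**The concern.** ML treats the fitted means as if they were known when it estimates variances, so the variances come out too small. The shortfall is negligible in a large trial but visible with 18 to 23 women per arm. REML removes it and uses incomplete records in the same way, so the missing-data purpose of the sentence gives no reason to prefer ML.

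Section 4.7 asks readers to look at effect sizes and intervals rather than tests. An interval that is too narrow overstates the precision of the signal passed to a later trial, and the error runs in one direction. Of the approaches named in section 4.9, the mixed model is also the one that uses partly observed women without filling in values. That makes it a plausible source of intention-to-treat intervals if dropout occurs.

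**Working it through.** **Inputs from the article.** Pooled variance 2.85, mean difference 1.83, Z values 1.96 and 1.28, dropout 20% (section 4.2.2); two arms; three time points (section 4.7).

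**Step 1: the plan's own sample size.** n = 2 × 2.85 × (1.96 + 1.28)² / 1.83² = 59.84 / 3.349 = 17.87, rounded up to 18 per arm. Then 18 / 0.8 = 22.5, rounded up to 23 per arm, or 46 in total. The stated figures reproduce. The relevant totals are N = 36 (evaluable) and N = 46 (randomised).

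**Step 2: ML against REML.** Take a model with a separate mean for each arm at each visit and complete data. ML divides the residual cross-products by N and REML divides them by N − 2, because each visit has two arm means. For the between-arm difference in change, the standard error ratio ML/REML is √((N − 2)/N).

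- N = 36: √(34/36) = 0.972, so the interval is 2.8% narrower. The ML variance is 94.4% of the unbiased value.
- N = 46: √(44/46) = 0.978, so the interval is 2.2% narrower. The ML variance is 95.7% of the unbiased value.

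The model has six cell means, but the correction for this contrast is two degrees of freedom, not six.

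**Step 3: coverage of a nominal 95% interval.** Coverage is P(|t| < ratio × quantile) on N − 2 degrees of freedom, with a ratio of 1 for REML.

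| Interval | N = 36 | N = 46 |
|---|---|---|
| ML, t quantile | 94.4% | 94.5% |
| ML, normal quantile | 93.5% | 93.8% |
| REML, normal quantile | 94.2% | 94.4% |
| REML, t quantile | 95.0% | 95.0% |

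**Step 4: splitting the larger figure.** At N = 36, an ML interval with normal quantiles has relative width 0.972 × 1.96 / 2.032 = 0.937, which is 6.3% narrower than REML with t. Of the two factors, ML gives 0.972 (2.8%) and the normal quantile gives 1.96 / 2.032 = 0.965 (3.5%). At N = 46 the combined ratio is 0.951.

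**Step 5: with dropout.** Random-intercept models were fitted by ML and by REML to simulated data with 20% of women missing later visits. The mean ratios were 0.968 starting from 18 per arm and 0.975 starting from 23 per arm. The second is the plan's own scenario. These runs used 25 data sets per setting, which is enough for the ratio but not for coverage.

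A larger simulation used 3,000 trials with 23 per arm, 20% dropout, unstructured covariance and an assumed between-visit correlation of 0.6. It gave 94.2% coverage for ML with t, 93.2% for ML with normal quantiles, and 94.6% for REML with t (Monte Carlo error 0.4–0.5 points). This agrees with the closed form.

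**Step 6: covariates, as an assumption only.** Section 4.8 allows adjusted models but fixes none. For a single-level model with p mean parameters the ratio is √((N − p)/N). With p from 4 to 8 this is 0.94 down to 0.88 at N = 36, and 0.96 down to 0.91 at N = 46.

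**The case against.** The strongest objection is about reach. A reader might infer that the trial's main intervals are all too narrow. The article does not support that. The mixed model is permitted rather than required, complete-case analysis is primary, section 4.7 offers ANOVA as an alternative and the abstract names it. ANOVA uses residual mean squares already corrected for degrees of freedom. No sentence ties the intervals of section 4.7 to an ML fit. This part of the objection stands in full.

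The second is about size. A reader might also infer a loss of 5–7% in width. That needs normal quantiles, which the article neither specifies nor excludes. The named estimator alone accounts for 2–3% of width and about half a point of coverage, in a trial that calls its analyses descriptive and its findings hypothesis-generating. This stands too, although being exploratory is not a reason to prefer the biased estimator when intervals are the intended output.

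The third is that, in a paragraph on missing data, maximum likelihood may mean likelihood-based methods in general, as opposed to imputation, and that degrees-of-freedom methods belong in an analysis plan that is not shown. The generic reading is possible. Followed literally, however, the sentence directs an ML fit, and that is a stated choice. The absence of a degrees-of-freedom method is not counted here as a fault.

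**Conclusion.** The point holds in a narrow form and at minor priority. If the mixed model of section 4.9 is fitted by ML as written, its 95% intervals for the between-arm difference in change will be about 2–3% too narrow, with about 94.4–94.5% coverage under t quantiles. Coverage would be 93.5–93.8% only if normal quantiles were used as well.

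These figures assume normal data, a separate mean for each arm and visit, no further covariates, and between 36 and 46 women. Dropout moves them only slightly; between-subject covariates would enlarge them. The complete-case results are not affected where they come from ANOVA, and nothing here shows that the trial's conclusions would change.

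**What to change.** In section 4.9, replace the reference to maximum likelihood with *restricted maximum likelihood estimation with Kenward-Roger or Satterthwaite degrees of freedom*, to apply wherever a mixed model is used, including under section 4.7. Naming the degrees-of-freedom method in the same phrase also settles the quantile question.

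The cost is one line of wording and a software setting, with no new data and no design change. Compared with ML and t quantiles, intervals widen by 1/0.972 − 1 = 2.9% at 36 women and 1/0.978 − 1 = 2.2% at 46. Compared with ML and normal quantiles, they would widen by 1/0.937 − 1 = 6.7% and 1/0.951 − 1 = 5.1%. Missing visits are handled in the same way as before.

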### 4.10 Safety

All adverse events (AEs) and serious adverse events (SAEs) will be systematically documented in the Case Report Form (CRF) using a predefined Adverse Drug Reaction (ADR) page. Each entry will capture the event description, diagnosis (if available), onset and resolution dates, severity (mild, moderate, or severe), action taken with the study drug (none, temporarily interrupted, or permanently withdrawn), outcome (resolved, resolved with sequelae, or not resolved), and the assessed relationship to the study drug (definite, probable, possible, unlikely, not related, or not assessable). The Principal Investigator and Co-Investigator will independently evaluate causality, taking into account the temporal relationship with the study drug, the participant’s clinical course, medical history, and concomitant medications. All adverse events will be followed until resolution or stabilization. Events occurring after a participant exits the study will not be routinely reported unless the investigators consider a reasonable likelihood of relation to the study drug, psychotherapy, or study procedures. This systematic documentation ensures continuous monitoring and prioritization of participant safety throughout the trial

